### Trial intervention

After randomisation, the patients will receive double-blind baclofen or placebo. Daily doses will be adapted to daily modification of the diet in renal disease (MDRD) creatinine clearance from 150 to 50 mg (see Table 1). On the day of randomisation, the patient will receive the full daily dose in a one-shot administration. Then daily doses will be divided into three intakes on the following days. During the mechanical ventilation period, the treatment/placebo will be administered via the nasogastric feeding tube. After extubation, the treatment will be administered either via the nasogastric tube or the oral route. The doses were determined after a preliminary pilot study and previous trial analysis regarding efficiency and safety data [25].

**Table 1 Tab1:** Doses of baclofen or placebo adjusted on daily assessment of the patient’s creatinine clearance

MDRD	D1 Loading dose	D2 and following days until extubation/tracheotomy at D15
Cl ≥90	150 mg	50-50-50
Cl 89–60	100 mg	30-20-50
Cl 30–59	70 mg	20-20-30
Cl <30 or continuous HD	50 mg	20-10-20
IHD	50 mg	50 mg before each session
Cl <15 without HD/IHD	50 mg	No administration

*Cl* renal clearance, *D* day, *HD* haemodialysis, *IHD* intermittent haemodialysis, *MDRD* modification of the diet in renal disease

The treatment will be tapered over a 7-day period after extubation or tracheotomy, or after the 15th day of treatment if the patient is still under mechanical ventilation. Treatment will be interrupted as described in Table 2.

**Table 2 Tab2:** Gradual interruption of baclofen or placebo after extubation or tracheotomy or on the 15th day of treatment

Dose administered on the day of extubation/tracheotomy/15th day	150 mg	100 mg	70 mg	50 mg	IHD 50 mg
Day +1	100 mg (20-30-50)	70 mg (20-20-30)	50 mg (10-20-20)	30 mg (10-10-10)	30 mg before dialysis (no administration if the patient is not dialysed)
Day +2	70 mg (20-20-30)	50 mg (10-20-20)	30 mg (10-10-10)	20 mg (10-0-10)	30 mg before dialysis (no administration if the patient is not dialysed)
Day +3	50 mg (10-20-20)	30 mg (10-10-10)	20 mg (10-0-10)	10 mg (10-0-0)	10 mg before dialysis (no administration if the patient is not dialysed)
Day +4	30 mg (10-10-10)	20 mg (10-0-10)	10 mg (10-0-0)	Stop	Stop
Day +5	20 mg (10-0-10)	10 mg (10-0-0)	Stop		
Day +6	10 mg (10-0-)	Stop			
Day +7	Stop				

*IHD* intermittent haemodialysis

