### Population

At ICU admission, patients with a mechanical ventilation (MV) duration expected to be equal to or longer than 24 h may be included.

For patients with tracheal intubation at ICU admission:If intubation was performed less than 48 h before admission, inclusion can be performed within 24 h after admissionIf intubation was performed 48 h or more before admission, inclusion cannot be performed

For patients without tracheal intubation at ICU admission:If intubation was performed within the first 48 h after admission, inclusion can be performed in the first 24 h after intubationIf intubation was performed at or after 48 h, inclusion cannot be performed

All patients, whatever the severity of organ failure, would be eligible for screening inclusion.

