### Primary outcome measure

Composite score: occurrence (yes or no) of agitation-related adverse events during treatment/placebo administration with at least one sign out of the following:Unplanned extubationMedical disposal removalFalling out of bedICU runawayImmobilisation device removalSelf-aggression or aggression towards medical staff

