### Protocol suspension and severe adverse reactions

The treatment could be discontinued:Temporarily if:○ Renal clearance falls below 15 ml/min without haemodialysis support○ Liver tests (amino-transferase enzymes) are more than 20 times the normal○ Heart rate falls below 50 BPM with haemodynamic consequencesDefinitively if:○ Allergic symptoms appear○ Heart rate falls below 35 BPM whatever the haemodynamic profile○ Non-reactive uni/bilateral mydriasis develops○ Patient has a seizure in the ICU○ Patient has a stroke in the ICU with computed tomodensitometry (CT) scan confirmation○ Eyes not open 72 h after total sedation is interrupted

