### Statistics

We hypothesised that baclofen administration can reduce the incidence of patients with at least one complication of agitation, using a two-sided test with an α of 5 % and 80 % power, from 42 to 27 %. This hypothesis in the placebo group is based on personal data. As a result, 314 patients are needed. Our study will include patients whatever their severity. Some patients may die before sedation interruption thus altering the power of the study. We therefore plan an interim analysis (after 50 % of inclusions), to adjust the sample size to maintain the statistical power. Friede and Kieser’s method [27, 28] allows both the initial hypothesis and the type-1 error planned a priori to be maintained. The analysis will be stratified at the participating centres. Statistical analysis will take place on an intention-to-treat principle. For the primary outcome, a logistic regression model will be applied to compare the proportion of agitation between the two treatment arms. Two sensitivity analyses will be performed and will consider dead patients to be without agitation, or as patients with or without agitation. A per-protocol analysis will also be performed to exclude patients with any of the exclusion criteria or without the inclusion criteria, or patients with incomplete treatment administration.

For the secondary outcomes, a Poisson regression model will be applied to compare the number of adverse events related to agitation, between the two treatment arms. Both length of ICU stay and mechanical ventilation will be compared with a log-rank test. Logistic regression will be used to compare binary qualitative secondary endpoints.

Normally distributed variables will be expressed as mean and standard deviation; nonnormally distributed variables will be expressed as median and interquartile range. Categorical variables will be expressed as numbers and percentages.

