### Track record

Data will be recorded in the web-based electronic case report form (eCRF) by trial site staff. Characteristics at baseline will be gathered: age, site of inclusion, sex, weight, height, medical history, reason for ICU admission, alcohol consumption, kidney function, Simplified Gravity Index (IGSII) and Sequential Organ Failure Assessment (SOFA) scores on admission. During ICU hospitalisation we will assess: cumulative doses of all sedative drugs, agitation and alcohol withdrawal scores, agitation-related adverse events, blood tests results regarding alcohol test on admission, liver function tests and blood count during treatment, acquired infection, length of ICU stay, mechanical ventilation and whole hospitalisation. To preserve confidentiality of participant’s personal information, data will be key-coded using alphanumerical numbers. To minimise missing data, primary and secondary outcome will be notified daily. Patients will be monitored until day 90 and a supplemental telephonic contact will promote complete follow-up.

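### The primary outcome counts agitation events only while study drug is given, so early drug stops that may differ by arm can bias the comparison in either direction

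*Protocol article*

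**What the plan says.** All references are to the protocol article.

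- **Primary outcome measure.** The endpoint is whether the patient has "agitation-related adverse events during treatment/placebo administration with at least one sign out of the following"; the listed signs include unplanned extubation, device removal and aggression. No calendar end is given.
- **Secondary outcome measure.** The first composite, agitation or 28-day death, uses the same drug-dependent window. The next item, agitation within 28 days of ICU admission, does not.
- **Trial intervention.** "The treatment will be tapered over a 7-day period after extubation or tracheotomy", or after treatment day 15 if the patient is still ventilated. The columns of Table 2 are set by "Dose administered on the day of extubation/tracheotomy/15th day", which follows renal function through Table 1.
- **Protocol suspension and severe adverse reactions.** Treatment may be paused (for example for low clearance without dialysis, or bradycardia with haemodynamic effect). It may also be ended for good. One such reason is "Patient has a seizure in the ICU"; others are a heart rate below 35 and failure to open the eyes by 72 h after sedation ends.
- **Statistics.** "Statistical analysis will take place on an intention-to-treat principle". The two sensitivity analyses concern patients who die. The per-protocol analysis removes patients with incomplete treatment.
- **Track record.** "During ICU hospitalisation we will assess: cumulative doses of all sedative drugs, agitation and alcohol withdrawal scores, agitation-related adverse events".

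**The concern.** The hypothesis is about agitation once sedation is lifted, so the days around and after extubation carry much of the information. If counting stops with the drug, a patient taken off treatment early remains in the analysis but cannot contribute a later event. Whether a patient is taken off is decided after randomisation, partly by reactions the drug may affect: slow heart rate, seizure, delayed waking. Randomisation does not balance such stops, and blinding does not remove an imbalance caused by the drug itself. An arm with more stops would show fewer counted events even if agitation were equally common in both.

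No planned analysis addresses this. The sensitivity analyses vary how deaths are classified, and the per-protocol analysis drops the affected patients instead of counting their later events.

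**Working it through.** **1. The plan's own figure.** Inputs from Statistics: 42% v 27%, two-sided 5%, 80% power, with 1:1 allocation. The mean rate is 0.345.

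n per arm = [1.960·√(2·0.345·0.655) + 0.8416·√(0.42·0.58 + 0.27·0.73)]² / 0.15² = 156.5, rounded up to 157, so 314 in total. The stated 314 is reproduced; power at 157 per arm is 80.1%.

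**2. Length of the taper window (Table 2).**

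| Dose when taper starts | Stop on day | Dosing days after extubation, tracheotomy or day 15 |
|---|---|---|
| 150 mg | +7 | 6 |
| 100 mg | +6 | 5 |
| 70 mg | +5 | 4 |
| 50 mg | +4 | 3 |
| Intermittent haemodialysis, 50 mg | +4 | at most 3, dialysis days only |

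An event on day +5 counts for a patient who was on 150 mg and not for one who was on 50 mg. Only the 150 mg column matches the 7-day taper described in the text.

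**3. Effect of unequal stops (illustration; the stop rates are assumed).** Suppose baclofen has no effect and the risk is 42% in both arms over a full window, with 157 per arm. Let s be the excess share of baclofen patients stopped early, at the same agitation risk as the rest. Let h be the fraction of their events that falls after the stop.

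Counted baclofen rate = 0.42·(1 − s·h); counted placebo rate = 0.42.

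The last column is the chance that a pooled z test at two-sided 5% is significant in favour of baclofen, from exact binomial probabilities.

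| s | h | Counted baclofen rate | False significant benefit |
|---|---|---|---|
| 0 | – | 42.0% | 2.4% |
| 5 points | 1 | 0.42·0.95 = 39.9% | 5.5% |
| 10 points | 1 | 0.42·0.90 = 37.8% | 11.4% |
| 5 points | 0.5 | 0.42·0.975 = 40.95% | 3.7% |
| 10 points | 0.5 | 0.42·0.95 = 39.9% | 5.5% |

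**4. The opposite direction.** The model is symmetric. With the excess stops on placebo and h = 1, the same 5.5% and 11.4% become chances of a false significant harm. If the hypothesised effect is real, a 5- or 10-point excess of placebo stops shrinks the counted difference from 15 points to 39.9 − 27 = 12.9 or 37.8 − 27 = 10.8 points.

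**The case against.** **The wording may mean the planned treatment period.** The Participant withdrawal section stops drug at once when consent is withdrawn, yet still allows primary outcome data to be collected and analysed if the patient does not object. That leaves some doubt that follow-up for this outcome ends at the last dose, although it could also refer only to data up to that point. This stands as a reason to call the problem a literal reading. It does not remove it, since the primary outcome definition should not depend on such an inference.

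**Intention to treat concerns who is analysed, and in which arm.** Correct: all randomised patients can still be analysed as allocated, and a reader who inferred that the plan breaks its own principle would go too far. The weakness lies in the endpoint, which the intention-to-treat label does not protect.

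**The illustration is near worst case.** Also fair. The definitive stop criteria are extreme, stopping is worded as permissible and not mandatory, and a patient who has not woken by 72 h is an unlikely source of self-extubation. The rows with h = 0.5 show how quickly the effect shrinks.

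**The bias need not favour baclofen.** This stands. The Background section links alcohol abuse to convulsions and cites reports that baclofen reduces withdrawal, so seizure stops could be commoner on placebo.

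**A 28-day agitation outcome is already planned.** It is a useful check, but it is secondary and does not change what the primary test compares.

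**Conclusion.** The point holds as a weakness in the primary endpoint that should be corrected. Read literally, the definition lets post-randomisation drug stops decide which events count, and those stops may differ by arm. The direction is open. The size cannot be determined, because the document gives no stop rates. The figures of 5.5% and 11.4% (3.7% and 5.5% with half the events after the stop) rest on assumed excess stops of 5 and 10 points, equal agitation risk in stopped patients and no true effect; they are illustrations, not estimates.

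Two stronger readings are not supported:

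- A reader might infer that the 3-to-6-day difference by renal dose biases the trial. Renal class should be balanced by randomisation, so this makes the endpoint uneven between patients but does not bias the arms.
- A reader might infer a loss of power. The document says only that the placebo rate comes from personal data and does not tie 42% or 27% to any window, so no loss is claimed.

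**What to change.** 1. In Primary outcome measure, and in the first composite of Secondary outcome measure, count agitation events in the ICU from randomisation over a window that does not depend on dosing. For example: to the end of day +7 after extubation, tracheotomy or treatment day 15, for every patient, whether doses were given, held or stopped.
2. Keep the on-treatment count as a sensitivity analysis.
3. Report the existing 28-day agitation outcome beside the primary result. The end of the proposed window is still tied to extubation, whose timing the drug may shift; the 28-day outcome is the check on that.
4. In Trial intervention, describe the taper as lasting up to 7 days according to Table 2.

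**Cost.** Changed wording and one extra analysis. The events are already recorded during the ICU stay. Under Population, the latest randomisation is 48 h + 24 h = 72 h after admission. Day +7 after treatment day 15 is treatment day 22, which is 21 days after the first dose, so about 3 + 21 = 24 days after admission and inside the 28 days already covered.

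**Downsides.** Some off-drug days are counted: day +7 only for a 150 mg patient, days +4 to +7 for a 50 mg patient. This may dilute the effect slightly. Events after ICU discharge remain uncaptured, as they are for the existing ICU-recorded outcomes.

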### Secondary outcome measure

Composite score: occurrence (yes or no) of agitation-related adverse events during treatment/placebo administration or 28-day mortalityAdverse event (yes or no) related to agitation within 28 days of ICU admissionNumber of adverse events related to agitation occurring during ICU hospitalisation within 28 days of ICU admissionRestlessness requiring rapid intravenous or intramuscular administration of hypnotic or neuroleptic drugs within 28 days of ICU admissionExtubation failure defined as reintubation within the next 48 hTracheotomy for failure of mechanical ventilation weaningInfections acquired in the ICU: urinary infection, pneumonia, catheter infection or bacteraemiaTotal doses of sedatives and painkillers received in the ICU within 28 days of ICU admissionRiker Sedation Agitation Scale (SAS) in the ICU within 28 days of ICU admissionDaily Clinical Institute Withdrawal Assessment of Alcohol Scale, revised (CIWA-Ar) alcohol withdrawal score during the week following extubationDuration of mechanical ventilationVentilation-free days (VFD) at day 28Length of ICU stayLength of total hospitalisationDeath in ICU, at days 28 and 90Death during hospital stay

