**Methods/design:**

This prospective, double-blind, randomised controlled study versus placebo will be conducted in twelve French intensive care units (ICU). Patients with an alcohol intake level higher than the NIAAA threshold, who are under mechanical ventilation, will be included. The primary objective is to determine whether baclofen is more efficient than placebo in preventing restlessness-related side effects in the ICU. Secondary outcomes include mechanical ventilation duration, length of ICU stay, and cumulative doses of sedatives and painkillers received within 28 days of ICU admission. Restlessness-related side effects in the ICU are defined as unplanned extubation, medical disposal removal (such as urinary catheter, venous or arterial line or surgical drain), falling out of bed, ICU runaway (leaving ICU without physician's approval), immobilisation device removal, self-aggression or aggression towards medical staff. Daily doses of baclofen/placebo will be guided by daily creatinine clearance assessment.

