### Randomisation and blinding

The clinicians will perform screening, enrolment and randomisation. Randomisation is centralised, web-based and accessible 24 h a day according to the allocation list on https://www.dirc-hugo-online.org/csonline/. Randomisation will be stratified at the centres using a fixed block size of 1:1 and a randomisation number will be allocated to each patient. Baclofen and placebo will be prepared and ‘blinded’ at Nantes University Hospital pharmacy. The independent trial statistician, patients, clinicians and nurses will be blinded for the allocation of treatment.

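### Five secondary outcomes are counted from ICU admission, up to 24 or 72 hours before randomisation, so they include events and doses that allocation could not have influenced

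*Protocol article*

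**What the plan says.** Under Secondary outcome measure, the protocol article sets a 28-day window starting at ICU admission for five items:

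- any agitation-related event, worded as "event (yes or no) related to agitation within 28 days of ICU" admission;
- the number of agitation-related events during the ICU stay;
- restlessness needing rapid injection of a hypnotic or neuroleptic;
- the total dose of sedatives and painkillers given in the ICU;
- the Riker Sedation Agitation Scale (SAS) in the ICU.

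The abstract repeats this origin for the dose outcome: "cumulative doses of sedatives and painkillers received within 28 days of ICU admission".

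Entry to the trial comes later than admission. Under Population, a patient already intubated on arrival may be included up to 24 h after admission. For the others, "If intubation was performed within the first 48 h after admission, inclusion can be performed in the first 24 h" following intubation. Under Trial intervention, study drug comes later still: "After randomisation, the patients will receive double-blind baclofen or placebo".

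The primary outcome has a different window. It is the "occurrence (yes or no) of agitation-related adverse events during treatment/placebo administration with at least one sign" from a list, so it covers the treatment period only.

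**The concern.** In a randomised comparison, an outcome should be counted from a point at which allocation can act on it. Here the clock for five outcomes starts before allocation exists. A patient not yet intubated can spend up to two days in the ICU, then up to one more day ventilated, before inclusion. If that patient removes a line or receives a rapid hypnotic injection in that time, the corresponding yes/no outcome is already positive at randomisation, and nothing that happens later can change it. Sedatives given in the ICU before randomisation likewise enter the cumulative dose.

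What is at stake is the sensitivity of these secondary comparisons. A real effect on agitation or sedative use would look smaller than it is. A fixed end at day 28 from admission also leaves patients with post-randomisation windows of different lengths.

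**Working it through.** **1. Maximum time from admission to randomisation** (Population; randomisation taken to occur at inclusion, since the article sets no separate interval)

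- Intubated on arrival: up to 24 h.
- Intubated in the ICU: up to 48 h to intubation + up to 24 h to inclusion = 72 h = 3 days.
- Share of the window: 72 / (28 × 24) = 72 / 672 = 10.7 %.
- Shortest post-randomisation window: 28 − 3 = 25 days, against 28 for a patient randomised at admission.

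**2. The plan's own sample size**

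Inputs from Statistics: "using a two-sided test with an α of 5 % and 80 % power, from 42 to 27" per cent, and "As a result, 314 patients are needed". Allocation is 1:1 (Randomisation and blinding). With the pooled-variance formula and no continuity correction, where p̄ = (0.42 + 0.27)/2 = 0.345:

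n per arm = [1.960 × √(2 × 0.345 × 0.655) + 0.842 × √(0.42 × 0.58 + 0.27 × 0.73)]² / 0.15²

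= [1.318 + 0.559]² / 0.0225 ≈ 156.5, rounded up to 157, so 314 in total.

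The stated figure is reproduced. Power at 157 per arm is 80.1 %. This calculation belongs to the primary outcome, whose window excludes pre-treatment events, so it stands as it is.

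**3. Illustration of dilution for a yes/no outcome**

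The article gives neither a 28-day agitation rate nor a pre-randomisation event rate. The illustration therefore borrows 42 v 27 % as the post-randomisation rates. It assumes a probability q of an event before randomisation, equal in the two arms and independent of later events. Each observed rate becomes 1 − (1 − q)(1 − p), and the difference becomes (1 − q) × 15 points. For q = 10 %: 1 − 0.90 × 0.58 = 47.8 % and 1 − 0.90 × 0.73 = 34.3 %.

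Power = Φ{[d√n − 1.960 × √(2p̄(1 − p̄))] / √(p₁(1 − p₁) + p₂(1 − p₂))}, with n = 157.

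| Assumed q | Placebo v baclofen | Difference (points) | Power |
|---|---|---|---|
| 0 | 42.0 v 27.0 % | 15.0 | 80.1 % |
| 2 % | 43.16 v 28.46 % | 14.7 | 77.8 % |
| 5 % | 44.90 v 30.65 % | 14.25 | 74.3 % |
| 10 % | 47.8 v 34.3 % | 13.5 | 68.3 % |
| 20 % | 53.6 v 41.6 % | 12.0 | 56.8 % |

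Under these assumptions any q above zero shrinks the absolute difference. How much depends on a rate that the article does not supply. No comparable figure can be given for the event count, the dose or the SAS, because the article states no distribution for them.

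**The case against.** Several points on the other side are sound.

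- **A reader might infer that the trial loses power from 80 % to 68 % or 57 %.** The article does not support this. The 42 v 27 %, the 80 % and the 314 belong to the primary outcome, which pre-randomisation events cannot enter. No power is claimed for any secondary outcome.
- **A reader might infer bias between the arms.** Events before randomisation cannot depend on allocation, and the trial is double-blind. The effect is dilution and noise, which works against finding a difference.
- **A reader might suppose that early agitation is common here and was often the reason for intubation.** The article gives no early-event rate and never names agitation as a reason for intubation. Hypothesis places the targeted agitation at the interruption of sedation, and an unplanned extubation cannot precede intubation. The 72 h limit applies to one entry route, and the mix of routes is not given. Low values of q must therefore be shown alongside high ones.
- **A reader might extend the point to ventilation-free days and to death at days 28 and 90.** The article states no time origin for these, so no error is shown there.
- **Unequal follow-up matters little for the treatment period.** Full dosing runs to day 15 at most and the taper ends by day +7, so treatment ends at about day 22. Adding a 3-day lag gives about day 25 from admission, still inside the window. Three of the outcomes (event count, dose and SAS) are also limited to the ICU stay.

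It could also be said that a condensed article leaves outcome details to the full protocol. That would answer a missing origin. Here the origin is stated, and nothing in the article excludes what happens before randomisation.

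**Conclusion.** The point holds for the five named secondary outcomes. As written, they count up to 24 h (intubated on arrival) or up to 72 h (intubated later) of ICU time before randomisation, assuming that randomisation occurs at inclusion. This weakens those comparisons and makes post-randomisation follow-up vary from about 25 to 28 days. It does not favour either arm and leaves the primary analysis and its sample size untouched.

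The windows follow directly from the text. The loss of sensitivity cannot be quantified from it: the power figures of about 78 to 57 % for q from 2 to 20 % rest on borrowed rates, equal early-event probability by arm and independence of early and later events. The point merits correction because the remedy is simple, but it does not threaten the trial's main conclusion.

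**What to change.** Define time zero for the five outcomes as randomisation and count from there to day 28 after randomisation, excluding earlier events and doses. Make the same change to the dose outcome in the abstract. Where the information is available, record agitation events and sedative dose between ICU admission and randomisation as baseline variables.

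The cost is small but not nil. Track record already provides for daily notification of outcomes and for follow-up to day 90, so no new visit is needed. Some patients would need up to 3 more days of daily recording. The baseline list in Track record does not include pre-randomisation agitation or sedative dose, so the baseline form would grow slightly. Events and doses on the day of randomisation would need to be placed before or after it.
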